#### Economic evaluation

For the CEA and CUA incremental cost-effectiveness ratios (ICERs) will be calculated, representing the differences in mean costs between the intervention and control group in the numerator and the difference in mean outcomes in the denominator. Sampling uncertainty around the ICER will be assessed by means of non-parametric boot-strapping (percentile method) [66]. The bootstrapped cost-effectiveness ratios will be subsequently plotted in a cost-effectiveness plane, in which the vertical line reflects the difference in costs and the horizontal line reflects the difference in effectiveness. The choice of treatment depends on the maximum amount of money that society is prepared to pay for a gain in effectiveness, which is called the ceiling ratio. Therefore, the bootstrapped ICERs will also be depicted in a cost-effectiveness acceptability curve showing the probability that ‘Stay Active at Home’ is cost-effective using a range of ceiling ratios. Additionally, to assess the robustness of the assumptions, multi-way sensitivity analyses will be performed. In the sensitivity analysis uncertain factors of assumptions in the base case analysis will recalculated to assess whether the assumptions have influenced the ICERs, for example by varying cost-prices and volumes between minimum and maximum.

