#### Clinical outcomes

The primary outcome measure for the CEA will be sedentary time. The primary outcome measure for the CUA will be generic quality adjusted life years (QALYs), measured by means of the standard newest Dutch version of the EuroQol-5D-5 L. (EQ-5D-5 L, [56, 57]). The EQ-5D-5 L consists of five dimensions of health-related quality of life, namely mobility, self-care, daily activities, pain/discomfort and depression/anxiety. Each dimension can be rated at five levels: ranging from ‘no problems’ to ‘major problems’ [58, 59]. The five dimensions can be summed into a health state. Utility values can be calculated for these health states, using preferences elicited from a general population, the so-called algorithm [60]. The utilities at the three time points (baseline and 6 and 12 months after baseline) will be used to calculate QALYs by means of the area under the curve method. In addition, the EQ visual analogue scale will be used to assess current health status [58, 59].

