This study has several strengths. First, the ‘Stay Active at Home’ programme was developed based on international evidence and in close collaboration with Dutch and foreign stakeholders [18]. Second, prior to the present study an exploratory trial was conducted (ClinicalTrials.gov: NCT02904889 (Smeets RGM, Kempen GIJM, Hansen WAG, Zijlstra GAR, van Rossum E, de Man-van Ginkel JM, et al. Experiences of home care professionals with the Stay Active at Home programme targeting reablement of community-living older adults. A qualitative study, submitted for publication)). The aims of this exploratory trial were to obtain experiences with the ‘Stay Active at Home’ programme and to test the study design. During the exploratory trial, challenges were identified which led towards some adaptations regarding the programme and the study design. For example, the exploratory trial showed that home care professionals did not identify with the interventionists, which is essential requirement for successful behavioural change according to behaviour change theory [72, 73]. Therefore, professionals who have already followed the ‘Stay Active at Home’ programme will be used as role models during the upcoming training sessions to share their experiences with their colleagues. The recruitment procedure was also adapted. In the exploratory trial, the participating nursing teams were asked to recruit older adults, resulting in a low response rate as nurses felt not responsible for the recruitment. In the proposed cluster randomised controlled trial, older adults will receive a short informational letter and flyer about the study as an announcement for a subsequent telephone call to assess whether they are potentially interested in participating in this study. Written informed consent will be obtained by the research team during the first home visit. Third, a strong aspect of the current study is that a combination of effect, economic and process evaluations will be conducted. Randomised controlled trials in the field of Reablement combining these different evaluations are scarce, yet important to obtain a complete picture. However, some limitations of this study must be acknowledged. First, it is not feasible in this study to objectively measure whether a behavioural change in home care professionals has taken place, as it is not possible to make use of (video) observations in the home care setting. Therefore, we rely on self-reported behaviour by home care professionals, which can result in biases due to social desirability and unaware/unskilled behaviour. Second, for this study, a follow-up period of 12 months has been chosen. This period may be too short to show effects, as home care professionals must first change their own behaviour before we can expect a behavioural change in older adults or changes in the consequent cost-effective outcomes with regard to their health and wellbeing. However, a longer follow-up is not possible due to practical and financial reasons.

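### A percentile bootstrap interval for the ICER cannot be interpreted if the QALY difference may change sign, and the plan has no provision for that case

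*Protocol article*

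**What the plan says.** The economic part of Data analyses fixes the uncertainty method for the ratio itself: "Sampling uncertainty around the ICER will be assessed by means of non-parametric boot-strapping (percentile method"). The replicates are then plotted on a cost-effectiveness plane, "in which the vertical line reflects the difference in costs and the horizontal line reflects the difference in effectiveness". Finally, "the bootstrapped ICERs will also be depicted in a cost-effectiveness acceptability curve", described as "showing the probability that ‘Stay Active at Home’ is cost-effective using a range of ceiling ratios".

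Two ratios are planned (Economic evaluation, Clinical outcomes). For the cost-effectiveness analysis (CEA): "The primary outcome measure for the CEA will be sedentary time". For the cost-utility analysis (CUA): "The primary outcome measure for the CUA will be generic quality adjusted life years (QALYs"). The text does not mention net benefit, a quadrant rule, or what is done if the effect difference crosses zero. The Discussion says of the 12-month follow-up: "This period may be too short to show effects".

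**The concern.** The percentile method sorts the replicates and cuts off the tails, so it assumes that a larger value always means a worse result, or always a better one. For an ICER this holds only while every replicate has an effect difference of the same sign. Once replicates lie on both sides of zero, equal ratios carry opposite meanings, and the ratio jumps from very large positive to very large negative values as the effect passes through zero. The 2.5th and 97.5th percentiles then mix opposite conclusions, and what they enclose is not a confidence interval for the cost per QALY.

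The CUA is the exposed analysis. The sample size rests on sedentary time, and no QALY difference is anticipated anywhere in the protocol. Cost-effectiveness is one of the trial's three aims, so an uninterpretable interval would stand beside one of its main results.

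**Working it through.** **No economic figure to reproduce.** The protocol gives no expected QALY difference, cost difference or SD for either. The one figure carried over is the number of completers per arm, from Sample size: 130 × (1 − 0.30) = 91. The planned sedentary-time effect reproduces: 0.15 × 535.9 = 80.4 min/day, and 80.4 / 145.7 = 0.55, as stated.

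**Step 1: ratios do not rank.** Take differences of EUR 1,000 and 0.02 QALY for illustration.
- Cheaper and better: −1,000 / +0.02 = −50,000.
- Dearer and worse: +1,000 / −0.02 = −50,000.
- Dearer and better: +1,000 / +0.02 = +50,000.
- Cheaper and worse: −1,000 / −0.02 = +50,000.

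The best and worst outcomes share one value, and the two trade-off outcomes share the other.

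**Step 2: how often the sign changes in the CEA.** With 80% power at two-sided 0.05, the planned effect is 1.96 + 0.84 = 2.80 standard errors from zero. The share of replicates with the wrong sign is Φ(−2.80), about 0.25%.

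**Step 3: how often it changes in the CUA.** The inputs are assumed: QALY SD 0.15 to 0.25, and true QALY gain 0 to 0.02. The standard error is SD × √(2/91) = SD × 0.148, that is 0.022 to 0.037 QALY, with clustering ignored. The share with a negative difference is Φ(−gain/SE):

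| QALY gain | SD 0.15 | SD 0.25 |
|---|---|---|
| 0.02 | 18% | 29% |
| 0.01 | 33% | 39% |
| 0 | 50% | 50% |

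**Step 4: what the percentile interval becomes.** Further assumptions are a cost difference of EUR +500, cost SD EUR 8,000 to 15,000 (SE about EUR 1,190 to 2,220) and no cost–effect correlation. Normal draws stand in for bootstrap pairs. Over the 12 combinations, the 2.5th percentile of the ratio lies between about minus EUR 0.4 and minus 1.3 million per QALY, and the 97.5th between about plus EUR 0.4 and plus 1.3 million.

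A second set of assumptions (SE 0.02 QALY, SE EUR 1,500, cost difference EUR +1,000) shows how the interval breaks down as the effect shrinks:

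| Effect / SE | Wrong sign | Percentile interval of the ratio (EUR per QALY) |
|---|---|---|
| 2.8 | 0.25% | −43,000 to 109,000 |
| 2 | 2.3% | −103,000 to 237,000 |
| 1 | 16% | −656,000 to 739,000 |
| 0 | 50% | −1.17 to 1.17 million |

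**Step 5: the acceptability curve.** Two counting rules can be compared at an illustrative ceiling of EUR 50,000: the share of ratios at or below the ceiling, and the share of pairs with 50,000 × effect difference − cost difference > 0. On the Step 4 grid the ratio-only share minus the net-benefit share is:
- cost difference EUR +500: +7 to +40 points;
- EUR −1,000: −6 to +10 points;
- EUR −2,000: −8 to −30 points;
- EUR −3,000: −13 to −44 points.

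The error exists only under the ratio-only rule, and its direction turns with the cost difference.

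**The case against.** The strongest reply is that the decision does not rest on an ICER interval. The protocol ties the choice of treatment to the ceiling ratio and goes from there to the acceptability curve. The plane and the curve show the quadrant information that an interval loses. This stands, and it limits the consequence. It does not repair the interval, because the percentile method for the ICER is a stated choice and not a detail left to a fuller plan.

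A reader might infer from the phrase "the bootstrapped ICERs will also be depicted in a cost-effectiveness acceptability curve" that the curve itself will be wrong. The protocol does not support that. It gives no counting rule, it defines the curve as a probability of being cost-effective, and the plane keeps cost and effect differences as pairs. A curve counted from those pairs has no error. A reader might also infer that the probability of cost-effectiveness would come out too high. That would require the ratio-only rule, and even then the sign depends on a cost difference the protocol does not give. Savings are as plausible as extra cost, since the Background cites studies with favourable results for care use and costs.

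It is also fair to say that the CEA is hardly touched at the planned effect. That stands, on condition that the planned effect occurs.

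**Conclusion.** The point holds for the percentile interval around the ICER, and mainly for the CUA. With 18% to 50% of replicates below zero QALY gain, the interval spans roughly minus EUR 0.4–1.3 million to plus EUR 0.4–1.3 million per QALY and cannot be read as a range of plausible values. These sizes rest on assumed SDs, QALY gains and costs, on independent participants and on uncorrelated costs and effects. The qualitative result needs only that the sign of the QALY difference is uncertain. In the CEA about 0.25% of replicates change sign if the planned effect on sedentary time occurs, and the problem would return there if the effect were small. The acceptability curve is not shown to be wrong, only loosely worded. The primary effect analysis is not affected.

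**What to change.** Replace the percentile interval on the ICER with incremental net monetary benefit (ceiling ratio × effect difference − cost difference) and its bootstrap percentile interval over the planned range of ceiling ratios. Net benefit is a linear function of the two differences, so it can be ranked whatever their signs. Keep the ICER as a point estimate, with the cost-effectiveness plane and the share of replicates in each quadrant. Reword the curve as the share of bootstrapped (effect, cost) pairs with net benefit above zero at each ceiling ratio. For the CEA, code a reduction in sedentary time as a gain.

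The cost is a few sentences in the economic analysis plan. The same replicates serve, and neither data collection nor design changes. The one downside is that no interval is quoted for the ICER itself.

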#### Process evaluation

For the process evaluation, a combination of quantitative and qualitative data analysis techniques will be used (need to be further specified).

### Research participation: ‘Nothing about us without us…’

To ensure a good match with the target group of the ‘Stay Active at Home’ programme, the experience of relevant stakeholders (i.e. home care professionals, older adults and informal caregivers) have been and will be incorporated in all research phases from pilot work until dissemination/implementation. By incorporating their experiential knowledge in research activities, findings are more likely to be relevant and the likelihood of successful implementation increases [67–69]. In addition, the project is embedded in the Living Lab of Ageing and Long-term Care www.academischewerkplaatsouderenzorg.nl), in which researchers and professionals from various disciplines closely collaborate to develop and disseminate evidence-based healthcare programmes [70].

Arnstein [71] differentiates between eight types of participation, which can be broadly categorised into 1) non-participation (i.e. therapy, manipulation); 2) tokenism (i.e. placation, consultation, informing); and 3) citizen power (i.e. citizen control, delegated power, partnership); Within this study, relevant stakeholders will be involved on different levels, depending on the phase of the project and the wishes of how the stakeholders want to be involved.

#### Informing

We will inform home care professionals and older adults during all phases of the research by making use of newsletters, articles, presentations and symposia. Furthermore, articles will be published in the journals of the involved health care organisation.

#### Consultation

The ‘Stay Active at Home’ programme is developed in close collaboration with relevant Dutch stakeholders (i.e. health care professionals, policy makers, managers, scientists) and a panel of older adults to ensure that all interests are considered and respected in the development [18]. Furthermore, first data about the feasibility of the ‘Stay Active at Home’ programme was collected during an exploratory trial (ClinicalTrials.gov: NCT02904889 (Smeets RGM, Kempen GIJM, Hansen WAG, Zijlstra GAR, van Rossum E, de Man-van Ginkel JM, et al. Experiences of home care professionals with the Stay Active at Home programme targeting reablement of community-living older adults. A qualitative study, submitted for publication)). During the proposed study, additional data from home care professionals and older adults will be collected as part of the process evaluation.

#### Placation

During the study two authors ([name] and [name]) will have continuously contact with different stakeholders from MeanderGroep South-Limburg (i.e. training officers, managers of nursing teams/domestic teams and district nurses) to make sure that the training fits with their working routines and to exchange experiences about the progress. In addition, a steering group will be created consisting of at least one representative from all collaborators (i.e. Maastricht University, Zuyd University of Applied Sciences, MeanderGroep South-Limburg, GP association in South Limburg (OZL General Practitioners), Burgerkracht, Dutch Nursing Association (V&VN)) and the research partners (also see the next paragraph). The steering group will meet twice a year to discuss the progress of the study and the dissemination/implementation of the results.

### Trial status

The recruitment of home care professionals started in September 2017. The first older adults were enrolled in October 2017. At the same time the data collection of the baseline data started. The last older adults will be recruited by the end of June 2018. Consequently, the last follow-up measurements will be conducted in June 2019. First results are expected by the end of 2019.

## Discussion

‘Stay Active at Home’ is a training programme that aims to equip home care professionals with knowledge, self-efficacy, skills and social support to deliver day-to-day services at home according to the principles of Reablement. This two-group cluster randomised controlled trial will be conducted to evaluate whether its implementation leads to a reduction in sedentary behaviour in older adults and thereby an increase in their level of physical activity. Furthermore, it will be investigated whether the programme leads to more cost-effective outcomes in terms of older adults’ health and wellbeing. In addition, an extensive process evaluation will be conducted alongside the trial. The process evaluation is of utmost importance to explain the results of the effect and economic evaluation.

This study has several strengths. First, the ‘Stay Active at Home’ programme was developed based on international evidence and in close collaboration with Dutch and foreign stakeholders [18]. Second, prior to the present study an exploratory trial was conducted (ClinicalTrials.gov: NCT02904889 (Smeets RGM, Kempen GIJM, Hansen WAG, Zijlstra GAR, van Rossum E, de Man-van Ginkel JM, et al. Experiences of home care professionals with the Stay Active at Home programme targeting reablement of community-living older adults. A qualitative study, submitted for publication)). The aims of this exploratory trial were to obtain experiences with the ‘Stay Active at Home’ programme and to test the study design. During the exploratory trial, challenges were identified which led towards some adaptations regarding the programme and the study design. For example, the exploratory trial showed that home care professionals did not identify with the interventionists, which is essential requirement for successful behavioural change according to behaviour change theory [72, 73]. Therefore, professionals who have already followed the ‘Stay Active at Home’ programme will be used as role models during the upcoming training sessions to share their experiences with their colleagues. The recruitment procedure was also adapted. In the exploratory trial, the participating nursing teams were asked to recruit older adults, resulting in a low response rate as nurses felt not responsible for the recruitment. In the proposed cluster randomised controlled trial, older adults will receive a short informational letter and flyer about the study as an announcement for a subsequent telephone call to assess whether they are potentially interested in participating in this study. Written informed consent will be obtained by the research team during the first home visit. Third, a strong aspect of the current study is that a combination of effect, economic and process evaluations will be conducted. Randomised controlled trials in the field of Reablement combining these different evaluations are scarce, yet important to obtain a complete picture. However, some limitations of this study must be acknowledged. First, it is not feasible in this study to objectively measure whether a behavioural change in home care professionals has taken place, as it is not possible to make use of (video) observations in the home care setting. Therefore, we rely on self-reported behaviour by home care professionals, which can result in biases due to social desirability and unaware/unskilled behaviour. Second, for this study, a follow-up period of 12 months has been chosen. This period may be too short to show effects, as home care professionals must first change their own behaviour before we can expect a behavioural change in older adults or changes in the consequent cost-effective outcomes with regard to their health and wellbeing. However, a longer follow-up is not possible due to practical and financial reasons.

## Abbreviations

ADL: Activities of daily living
CEA: Cost-effectiveness analysis
CG: Control group
CUA: Cost-utility analysis
DSM-IV: Diagnostic and Statistical Manual of Mental Disorders, 4th Edition
DSWs: Domestic support workers
EQ-5D-5 L: EuroQol-5D-5 L
GARS: Groningen Activity Restriction Scale
Hz: Hertz
IADL: Instrumental activities of daily living
ICERs: Incremental cost-effectiveness ratios
IG: Intervention group
iMTA: Institute for Medical Technology Assessment
LASA: Longitudinal Aging Study Amsterdam
MRC: Medical Research Council
N/A: Not applicable
PHQ-9: Patient Health Questionnaire 9
QALYs: Quality adjusted life years
SD: Standard deviation
SPIRIT: Standard Protocol Items: Recommendations for Interventional Trials
SPPB: Short Physical Performance Battery
SPSS: Statistical Package for the Social Sciences
T0: Baseline
T1: Follow-up 1
T2: Follow-up 2
UK: United Kingdom
US: United States
